# Adjunctive duration-doubled transcranial direct current stimulation for the treatment of depressive patients with suicidal ideation: study protocol for a double-blind, randomized, sham-controlled trial

**DOI:** 10.1186/s13063-023-07858-0

**Published:** 2024-01-02

**Keywords:** Transcranial direct current stimulation (tDCS), Major depressive disorder (MDD), Suicidal ideation, Randomized controlled trial (RCT)

## Abstract

**Background:**

The problem of suicide has become increasingly common in individuals with major depressive disorder (MDD). Transcranial direct current stimulation (tDCS) is an effective treatment for MDD with 2 milliamperes (mA) for at least 30 min per day for 2 weeks. This study aims to investigate the efficacy of daily duration-doubled tDCS as an adjunctive intervention for rapidly reducing suicidal ideation and improving depression in MDD patients.

**Methods:**

In this double-blind, randomized, sham-controlled study, 76 MDD patients with suicidal ideation are randomly assigned to either active (*n*=38) or sham (*n*=38) tDCS group. The anode and cathode are placed over the scalp areas corresponding to left and right dorsolateral prefrontal cortex (DLPFC), respectively, and each stimulation lasts for 60 min. The primary outcome is defined as change of Beck Scale for Suicide Ideation (BSI) after 5 and 10 sessions. The change of other clinical assessments, blood biomarkers related to suicidal ideation and depressive sumptoms are defined as secondary outcomes. Blood biomarkers related to suicidal ideation are collected at baseline and after 10 sessions.

**Discussion:**

This study suggests the adjunctive duration-doubled tDCS might be a novel method to rapidly reduce suicidal ideation and improve depressive symptom. The variation of biomarkers could be potential predictive models of suicide risk.

**Trial registration:**

The trial protocol is registered with ClinicalTrials.gov under protocol registration number NCT05555927. Registered on September 25, 2022.

**Supplementary Information:**

The online version contains supplementary material available at 10.1186/s13063-023-07858-0.

## Administrative information

This protocol was written in accordance with the Standard Protocol Items: Recommendations for clinical Interventional Studies (SPIRIT) guidelines [1]. Note: the numbers in curly brackets in this protocol refer to SPIRIT checklist item numbers. The order of the items has been modified to group similar items (see http://www.equatornetwork.org/reporting-guidelines/spirit-2013-statement-defining-standard-protocol-items-for-clinical-trials/).

## Introduction

### Background and rationale {6a}

Depression is a common mental disorer. Globally, it is estimated by the World Health Organization that 5% of adults suffer from depression. During the last decade, the problem of suicide has become more serious in individuals with major depression disorder (MDD). It is important to track whether alternative or adjunct treatment strategies have the potential to rapidly and effectively reduce suicide risk. Among brain stimulations, transcranial direct current stimulation (tDCS) has been proposed as a possible interventional tool. Over the past decade, trials [2, 3] and meta-analyses [4, 5] have shown mixed, albeit positive, results for tDCS as a treatment for MDD. However, trials or meta-analyses that analyzed the factor structure of depression, described as ‘suicide risk’, ‘suicide attempt’ or ‘suicidal ideation’ were rare.

On the other hand, until recently, the bulk of the literature into suicide-focused interventions centered around suicide attempts, particularly on preventing reattempt over the 6- to 12-month period after the index attempt [5]. In such trials, suicidal ideation is usually tracked as a secondary outcome measure. In contrast, evaluating rapid-acting interventions for suicidal ideation requires randomized clinical trials (RCTs) that focus on suicidal ideation as a primary outcome. Therefore, we highlight potential changes that could be made to clinical trials for suicidal ideation in the specific areas of participant selection, outcome measurement, and serum mechanisms of change.

Next, tDCS could be an effective method on depressive symptoms with a current of 2mA, 30 min per daily session and a therapeutic period of at least 2 weeks [6]. Near-linear effects of stimulation intensity (0.2 to 2.0 mA) and duration (from 1 to 13 min) were found on physiological effects of tDCS stimulation in motor cortex [7]. Since these early studies [7, 8], there has been a tendency in tDCS research to study the effects of increased duration or intensity of stimulation with the expectation of increased efficacy in behavioral and neurophysiological outcome measures. What is more, the excitement surrounding noninvasive neurostimulation as an adjunctive rapid-acting antidepressant with antisuicidal effects presents an important opportunity for framing studies in suicide research. In addition to offering an opportunity to evaluate the effects of tDCS as an adjunctive rapid-acting intervention on suicidal ideation and suicide risk, such initiatives could help researchers explore potential biomarkers of response and, ultimately, develop better treatments.

What is more, in recent years, a wide range of possible biological risk factors for suicide have also been proposed. As some recent trials demonstrated, systematic inflammation, indicated by increased levels of white blood cell (WBC) count or serum C-reactive protein (CRP), was also associated with later risk of suicide [9, 10]. Two studies even suggested that neutrophil-to-lymphocyte ratio (NLR) may be a marker for suicide vulnerability in patients with MDD [11, 12]. NLR was substantially higher in suicidal depressed patients compared with nonsuicidal depressed patients and healthy controls. One logistic regression model included NLR and previous attempts as predictive variables for suicide status [11]. What is more, NLR, monocyte-to-lymphocyte ratio (MLR), platelet-to-lymphocyte ratio (PLR), nerve growth factor (NGF), brain-derived neurotrophic factor (BDNF), glial cellline-derived neurotrophic factor (GDNF), interleukin (IL), soluble tumor necrosis factor receptor I (sTNFr1), and soluble tumor necrosis factor receptor II (sTNFr2) have been found to be associated with MDD [12, 13] as compared with healthy controls [14]. However, we are still far from having good biomarkers for either suicidal ideation or suicide attempt. Moreover, these possible biological risk factors were no more further investigated during or after certain antisuicidal treatment. And the possible association of their variation and suicide status change was not yet reported.

Therefore, any rapid-acting strategy for suicidal ideation has the potential to lead to new developments in clinical trial and to generate valuable clinical and research considerations for the field as a whole. Daily high-dose repetitive transcranial magnetic stimulation (rTMS) could be a novel and safe method for rapidly improving suicidal ideation in treatment-naive patients with MDD [15]. While most tDCS researches have focused on its antidepressive mechanisms, the field of preventing suicide is expanding to encompass important psychological considerations related to tDCS use that warrant discussion, including the best way to measure changes in suicidal ideation and the treatment of the suicidal individual. The present study will investigate the effects of daily duration-doubled tDCS as an adjunctive intervention for rapidly improving suicidal ideation and depression in MDD patients with antidepressants.

### Objectives {7}

The primary objective of this study is to investigate the acute efficacy on suicidal ideation, measured by the Beck scale for Suicidal Ideation (BSI) score. We hypothesize that a higher efficacy and larger reduction in suicidal ideation will be observed in tDCS group than sham group after 1 and 2 weeks when tDCS performed as an adjunctive treatment.

The secondary objectives include:To investigate the acute improvement on other clinical measurements, measured by the 17-item Hamilton Depression Rating Scale (HAMD-17) score, etc., of duration-doubled tDCS or sham tDCS, after 1 and 2 weeks.To investigate the potential association among variation of WBC, CRP, NLR, MLR, PLR, NGF, BDNF, GDNF, IL, TNF-α, sTNFr1, sTNFr2 and suicidal ideation as well as depressive symptoms in MDD patients [11–13] treated by adjunctive tDCS.To investigate the clinical relevance of tDCS efficacy and side effect occurence.

### Trial design {8}

The design of the trial is a double-blinded, randomized, sham-controlled trial to test for the superiority of the active tDCS group versus sham group. MDD patients, who took no psychotropic drug at baseline or maintained actual pharmacotherapy for at least 2 weeks before the stimulation initiation and during the whole stimulation period, were included. Groups will be randomized through a random code generator software (REDCap) at ratio of 1:1 into one of the following two groups: tDCS group or sham group. The total study duration is 8 weeks (Fig. 1).

**Fig. 1 Fig1:**
[figure not shown]
Trial flowchart. We plan to recruit 76 patients with MDD. For the patients who take no psychotropic drug at baseline or maintain actual pharmacotherapy for at least 2 weeks before the stimulation initiation and during the whole stimulation period. The patients will be randomized (1:1) into one of the following two groups: tDCS group or sham group. Primary and secondary study parameters will be accessed at baseline (week 0), the 1st week (after 5 sessions), 2nd week (after 10 sessions), 4th week (2 weeks after intervention), 6th week (4 weeks after intervention), and 8th week (6 weeks after intervention)

## Methods: participants, interventions, and outcomes

### Study settings {9}

We will approach patients at the Shanghai Mental Health Center outpatient and inpatient units by advertisement.

### Recruitment {15}

We will approach patients at the Shanghai Mental Health Center outpatient and inpatient units. Our inpatient and outpatients’ care unit follows at least 10,000 patients with MMD each year. Considering the inclusion and exclusion criteria, we expect approaching 100 patients to recruit 76 patients. Usual clinical care will be maintained for all patients following completion of the trial at our care unit. A well-trained group is involved in the participant enrolment process, including one senior psychiatrist, one PhD student, one MD student, eight master students working full-time, and ten psychiatrists who refer patients for scientific research. We provide the participants and their guardians with a thorough explanation to ensure that they fully understand the study.

Recruitment, pre-participation screening, allocation, intervention, and data collection will occur between September 2022 and March 2024. We plan that the study will be concluded, and the results will be available for analysis at the end of 2024. The present study protocol complies with the SPIRIT 2013 recommendations (Standard Protocol Items: Recommendations for International Trials) [1] (see Additional file 1). Figure 1 shows the schedule of enrollment, interventions, and assessments.

### Eligibility criteria {10}

#### Inclusion criteria

Ages are from 18 to 50;Meeting the criteria of the Diagnostic and Statistical Manual of Mental Disorder (DSM-5) for current unipolar MDD, which is assessed by at least one professional psychiatrist;Han ethnicity;Right handedness;With a score≥17 on the HAMD-17 [16];With a score≥6 on the BSI [17];Without any pharmacotherapy at baseline or maintaining actual pharmacotherapy for at least 2 weeks before the stimulation initiation and during the total stimulation period.

#### Exclusion criteria

Assessed through applying the Mini-International Neuropsychiatric Interview (MINI) [18] by professional psychiatrists that diagnosed any other current or past psychiatric axis-I disorders (except MDD in the patients);Severe liver and kidney diseases, active endocrine diseases or clinical symptoms. Severe cardiovascular disease, respiratory system disease, haematologic diseases, and cancer;Any clinically significant abnormal laboratory examination that may influence the health of participants;A history of any significant medical illness such as neurological disorders (such as cerebral trauma and seizure disorder);Known current psychosis as determined by the DSM-5 or a history of a non-mood psychotic disorder;Current alcohol and drug abuse;Current or planned pregnancy and/or lactation during the trial;Abnormal scalp such as open wounds;HAMD-17 item 3 (suicide) score=4;Receiving modified electroconvulsive therapy (MECT) or rTMS in the past 1 month;Participation in another clinical trial concurrently or no more than 1 month prior to randomization.

### Who will take informed consent? {26a}

The assessors will obtain written consent from all participants.

### Additional consent provisions for collection and use of participant data and biological specimens {26b}

On the consent form, the patients can decide to accept being collected plasma to test biomarkers and being contacted in the future regarding the results of the biomarkers. Patients who decline this option still participate in the study.

## Interventions

### Background and rationale: choice of comparators {6b}

Sham group has been chosen as the comparison group. See below item 11a.

### Intervention description {11a}

Participants will receive one of two interventions: tDCS group or sham group. For brain stimulation, tDCS-CT devices (Neuroelectrics, Starstim 8, USA) are used. The stimulation protocol A or B will be administered in a software matched by tDCS device and by a staff member outside the research group with password. The research group cannot obtain the password during the trial. The participants will receive tDCS stimulation of protocol A or B as randomized from start to finish. The anode and cathode electrodes are inserted in saline-soaked sponges with diameter of 3.2cm and then positioned over the left and right dorsolateral prefrontal cortex (DLPFC) using specific headgear [19]. Each session uses a 2mA current and lasts 60 min. Ten sessions are daily performed on weekday. For sham, the current rapidly ramp up to 2mA over the first 30s and rapidly ramped down to 0mA over the next 30s automatically to allow participants to feel typical initial sensations of active tDCS [20, 21]. Trained psychiatrists and psychologists blind to group assignment administered the tDCS regimen. After completing ten sessions, no treatment is interdictory.

### Criteria for discontinuing or modifying allocated interventions {11b}

If participants do not meet the inclusion criteria;If participants or their guardians decide to leave the study;If participants develop a serious physical disease whether or not it is related to tDCS;If participants stop taking their medication for three consecutive days, stop effective contraception or become pregnant;If participants use other treatments (including MECT, rTMS);If other conditions occur, and the investigator decides to terminate the study;Defaulting.

During 10 sessions, modification of dose is not permitted. When ceasing treatment, no treatment is interdictory and participants could follow psychiatric routine.

### Strategies to improve adherence to interventions {11c}

During the intervention, every session is completed by tDCS-CT devices (Neuroelectrics, Starstim 8, USA) conducted by Neuroelectrics’ software according to the result of randomization as group A or B. Sessions are recorded in one document, including starting and ending time, name of operator, adverse effect of each session. Process of each session was performed as the same.

### Interventions: concomitant care {11d}

The participants in the study are not permitted to participate in other trials during the 2-week’s interventions. Most patients will receive concomitant individual pharmacotherapeutic treatment during this 2-week’s interventions.

### Provisions for post-trial care {30}

No provisions for post-trial care are planned. Patients could follow psychiatric routine after the completion of 10 sessions.

### Outcomes {12}

#### Primary outcome

The primary outcome is defined as reductive ratio of BSI after 1 and 2 weeks, as well as, after 5 and 10 sessions.

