### Sample size {14}

The sample size was calculated based on the data from Kalu et al. [22] and Boggio et al. [23]. In these studies, the active tDCS was assumed to be superior to sham tDCS in controlling depression with a conservative mean diference of 0.74 and standard deviation (SD)=25.8. We set the type 1 error, *α* (significance), and the a power at 80%. We used G power software (V.3.1.9.4) to calculate the sample size. The result indicated that a minimum of 30 patients per group are needed (a total of 60 patients). Considering the 20% drop-out rate, 75 patients are needed in our experiment. Finally, we planned to enrol 38 patients per group for a total of 76 included patients.

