## Data collection methods

### Plans for assessment and collection of outcomes {18a}

#### Primary study parameter/endpoint

##### BSI

The primary outcome criterion is the reductive ratio in BSI score after 1 and 2 weeks of the treatment. A treatment response is defined as a 50% reduction in the BSI score and remission is defined as score of 6 in the BSI at any point during the 8-week trial compared with the baseline.

Secondary study parametersMini-International Neuropsychiatric Interview (MINI);HAMD-17, MADRS, and ODQ;YMRS;CGI;SDS;WCST and SCWT;Peripheral venous blood: Biomarkers representing inflammatory mechanisms associated with suicidal ideation and MDD are assessed. (1) Routine tests: The routine tests include calculation of the WBC, CRP, neutrophils, lymphocytes, monocytes, platelets. (2) Specific tests: We collect the peripheral blood serum and store it at −80°C after centrifugation. We examine the NGF, BDNF, GDNF, IL, TNF-α, sTNFr1, sTNFr2. NLR, MLR, and PLR in serum using ELISA.

Data collection will be performed by staff of study who will be trained in how to do assessments. Participants will be familiarized with the equipment and tests of study during screening. For all participants, data collection will be conducted at a certain time, in face-to-face meetings. The peripheral blood collection will be done at the laboratory in Shanghai Mental Health Center.

Participants will receive a SMS text or an email to remind their appointment the day before. PI (YC) of the study will supervise data collection to check the quality, completeness, plausibility, and possible errors of the collected data.

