## Statistical methods

### Statistical methods for primary and secondary outcomes {20a}

Descriptive analysis will consist of means and SD for continuous variables and percentages for categorical variables. Data normality will be tested with the results expressed as mean ± SD or percentage, whenever appropriate. Non-parametric tests will be used if data were not normally distributed. Baseline variables will be compared between the groups using either the Student *t* test or chi-squared test (e.g., sociodemographic data, cognitive function data, biomarkers representing inflammatory mechanisms associated with suicidal ideation and MDD, response and remission rates between groups). To compare primary endpoint, a two-way ANOVA will be used considering group (intervention and sham-control groups) and time points (pre and post-intervention), followed by the Bonferroni post hoc test, in case of significant F ratios. Using a mixed-effects model for repeated measures to analyze change from baseline of BSI scores, time, and their interaction. We will also adopt pretreatment values (e.g., age, gender, baseline BSI, HAMD-17, CRP, and blood cells level) as covariates to correct the possible differences. An intention-to-treat analysis will be conducted, i.e., all participants, regardless of adherence to the intervention, will be included in the final analysis. All calculations will be performed using the R-softawre, and the significance level will be set at *P* ≤ 0.05.

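### No success rule is fixed for the two primary time points (week 1 and week 2), so neither 5% type I error nor 80% power can be confirmed

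*Protocol article*

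**What the plan says.** - **Endpoint.** The outcomes section (item 12) gives this definition: "The primary outcome is defined as reductive ratio of BSI after 1 and 2 weeks, as well as, after 5 and 10 sessions". The data collection section (BSI) repeats this: "The primary outcome criterion is the reductive ratio in BSI score after 1 and 2 weeks of the treatment". The abstract also lists both visits.
- **Hypothesis.** Objectives {7} expects that a "larger reduction in suicidal ideation will be observed in tDCS group than sham group after 1 and 2 weeks".
- **Sample size.** Sample size {14} works from a "conservative mean diference of 0.74 and standard deviation (SD)=25.8", then says "We set the type 1 error, *α* (significance), and the a power at 80" per cent. No value is printed for alpha. The result is 30 per group, 75 in total after 20% dropout, and 76 enrolled (38 per group).
- **Analysis.** Statistical methods {20a} compares the primary endpoint by a two-way ANOVA of group by time, with time described as pre and post intervention. Bonferroni post hoc tests follow a significant F. A mixed model for repeated measures on change in BSI is also named, without a target visit or contrast. The threshold is general: "the significance level will be set at *P* ≤ 0.05".

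No section ranks the two visits or says whether one or both must favour active stimulation.

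**The concern.** With two primary visits, the type I error and the power are defined only once the success rule is known. The either-visit and both-visits rules behave differently, and the protocol was sized for neither: its calculation has one comparison.

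The two results could well split. Week 1 carries the claim of rapid action, and week 2 reflects the full course of 10 sessions. If only one visit is significant, the present text allows the trial to be called positive (either suffices) or negative (both needed), and that choice could be made after the data are seen. Interim analyses {21b} adds to this, because it plans interim looks at the primary endpoint and gives the research team access to the results.

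**Working it through.** **Inputs from the protocol.** Effect 0.74, power 80%, 30 per group before dropout, 20% dropout and 38 per group enrolled (Sample size {14}); significance level 0.05 (Statistical methods {20a}); 1:1 allocation (Trial design {8}).

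**Assumptions.** Two-sided alpha of 0.05 in the sample size. The value 0.74 is a standardised effect d: read literally against an SD of 25.8 it would need 19,082 per group. The same d applies at both visits unless stated. The correlation ρ between the two test statistics is not given; 0.5 to 0.8 is used.

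**Step 1: reproduce the plan's figure.** For a two-sample t test, the noncentrality is d·√(n/2) = 0.74 × √15 = 2.866 on 58 degrees of freedom. Power is 80.5%, and 30 is the smallest n per group that reaches 80%. A one-sided test would need only 24. Dropout: 60 / (1 − 0.20) = 75. So the plan's figures match one two-sided comparison at 0.05, with no allowance for a second visit.

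**Step 2: apply each possible rule.** Treat (Z1, Z2) as bivariate normal with correlation ρ. The means are 0 under the null, 2.866 with 30 per group, and 0.74 × √19 = 3.226 with 38 per group.

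- (a) Either visit, unadjusted. Error = 1 − P(|Z1| ≤ 1.96 and |Z2| ≤ 1.96).
- (b) Both visits required. Power = P(Z1 > 1.96 and Z2 > 1.96).
- (c) Either visit, 0.025 each. As (a), with critical value 2.241.

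| Rule | Quantity | ρ = 0.5 | ρ = 0.7 | ρ = 0.8 |
|---|---|---|---|---|
| (a) | Type I error | 9.1% | 8.3% | 7.8% |
| (b) | Power, 30 per group | 71.1% | 73.5% | 75.1% |
| (b) | Same, t critical value (58 df) | 69.6% | 72.1% | 73.7% |
| (b) | Power, 38 per group | 82.8% | 84.3% | 85.2% |
| (c) | Type I error | 4.6% | 4.3% | 4.0% |
| (c) | Power to win at least one visit, 30 per group | 86.8% | 83.7% | 81.8% |

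The normal approximation is slightly generous. For one comparison it gives Φ(2.866 − 1.960) = 81.8%, against 80.5% from the t test.

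Under (c), if the effect exists at one visit only, the t test at that visit has 71.3% power with 30 per group. Reaching 80% there would take 37 per group, or 74 / 0.8 = 92.5, so 93 in total, against 76 planned.

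**Step 3: a fixed order.** The first-ranked visit is tested at 0.05 and the second only if the first is significant. Family-wise error is at most 5%, and power at the first visit is the planned 80.5%. The chance of claiming both visits is that of rule (b).

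**The case against.** A reader might infer that each visit is tested separately at 0.05, so that either the 5% or the 80% must fail. The document does not support that reading, for these reasons.

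- **No section says each visit is tested at 0.05.** The threshold is a general one. A single group-by-time test is a possible reading of the primary analysis, and Bonferroni tests are named after a significant F.
- **Bonferroni may be meant to cover both visits.** The protocol does not say whether its post-intervention level is one visit or two. It cannot be said that the step fails to cover them, only that it is not tied to them.
- **The two failures are not the only outcomes.** Rule (c) keeps error below 5% and gives 82% to 87% power to win at least one visit, if the effect is equal at both.
- **The word joining the visits in Objectives {7} may mean both are required.** Then there is no inflation of type I error.
- **The shortfall under rule (b) needs the full 20% loss.** With all 38 per group evaluable, power is 83% to 85%. The plan is intention-to-treat with multiple imputation, although imputation does not recover all the information lost, so 38 is the upper bound.

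All of this stands and narrows the point. It does not remove it, because each defence supplies a rule that the protocol does not state. Nor can the gap be left wholly to an unseen analysis plan. The detailed multiplicity procedure may sit there, but which visit decides the trial is part of the endpoint definition, which this document gives as two visits while sizing for one comparison.

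**Conclusion.** The concern holds in this form: the protocol makes BSI reduction at weeks 1 and 2 jointly primary, fixes no decisive visit or success rule, sizes for one comparison, and does not connect its Bonferroni step to the two treatment contrasts. Neither the 5% error nor the 80% power can be confirmed.

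It does not follow that one of them is certainly broken. The size depends on the rule: 7.8% to 9.1% type I error under unadjusted either-visit success, and about 70% to 75% power under both-required success with 30 evaluable per group. Under 0.025 each with either visit sufficing, both targets are met for equal effects.

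These figures rest on ρ of 0.5 to 0.8 and, for power, on d = 0.74 at both visits. The protocol gives neither for BSI; its 0.74 comes from depression outcomes. Any error added by the interim looks is a separate matter and is not counted here.

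**What to change.** Before any unblinded or interim look, amend Outcomes {12}, the BSI paragraph and Statistical methods {20a} so that they agree on:

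1. one primary time point, for example week 2 (after 10 sessions), with its treatment contrast tested two-sided at the full 0.05;
2. the other visit tested at 0.05 only if the first is significant;
3. what, if anything, the Bonferroni tests apply to.

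If rapid onset is the main claim, week 1 may come first, but the order must be fixed in advance. State the alpha value in Sample size {14} and name the time point to which the calculation refers.

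The cost is protocol wording. The planned 76 can stay, because power at the first-ranked visit is unchanged at 80.5% under the plan's own assumptions. The downside is that the second-ranked visit cannot be claimed if the first fails. If the sponsor prefers 0.025 at each visit with either sufficing, that is also valid once written down, but power is about 71% when the effect is present at only one visit.
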